### Serious Adverse Device Effect (SADE)

Serious adverse device effect (SADE) is any adverse event that meets the serious criteria as per the TGA [Therapeutic Goods (Medical Devices) Regulations 2002](https://www.legislation.gov.au/Series/F2002B00237) section 5.7

Any of the following device related adverse events will therefore be reported to the manufacturer:

- death of a patient, health care provider, user or other person; or
- a serious injury or serious deterioration to a patient, health care provider, user or other person, including;
- a life-threatening illness or injury;
- permanent impairment of a body function;
- permanent damage to a body structure; or
- a condition necessitating medical or surgical intervention to prevent permanent impairment of a body function or permanent damage to a body structure.
- near adverse event, it is sufficient that:
- an event associated with the device occurred; and
- if the event occurred again, it might lead to death or serious injury as outlined above.

### Event Relationships

Investigators will report the relationship of each event to the study device or procedure.

| Procedure related | An adverse event which, in the judgment of the Investigator, results as a consequence of the procedure and is not specifically related to use of the device. |
| --- | --- |
| Device related | An adverse event which, in the judgment of the Investigator, results as a consequence of the use of the device and is not specifically related to the treatment procedure |
| Unrelated | The adverse event is clearly not related to the device or procedure - i.e. another cause of the event is most plausible;  and/or a clinically plausible temporal sequence is inconsistent with the onset of the event. |

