## **CorPath GRX**

### Intended Use & Device Description

The CorPath GRX is intended for use in the remote delivery and manipulation of guidewires and rapid exchange balloon/stent catheters, and remote manipulation of guide catheters during percutaneous coronary intervention (PCI) procedures.

The CorPath GRX System is designed to allow the interventional cardiologist to remotely manipulate guidewires, rapid exchange balloon/stent catheters and guide catheters within a participant’s vasculature to perform PCI procedures in a precise and well-controlled fashion, without being exposed to radiation levels typically encountered during a conventional (i.e., manual) PCI. The CorPath GRX System is composed of a Remote Workspace and a Bedside Unit.

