## **Adverse Events, Event Assessment and Serious Adverse Device Events**

### Adverse Events (AEs)

Study staff will closely monitor each participant for the development of device and/or procedure related adverse events. Adverse events that meet this criteria will continue to be monitored until day 30 or until resolution or the investigator deems them stable and unresolved.

Adverse Events of Special Interest (AESI) are those defined as MACE including cardiac death, clinically relevant MI after coronary revascularization (Q-wave or non-Q-wave myocardial infarction), or clinically driven target vessel revascularization (TVR).

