**Procedure-Related Adverse Event**

An adverse event is procedure-related when, in the judgment of the Investigator, it is reasonable to believe that the event is not associated with the CorPath GRX System use. Instead, other products, surgical techniques, or medications required specifically for the procedure are deemed by Investigator as likely to have contributed to the occurrence of the event.

**Abrupt Closure:** The occurrence of new severely reduced flow (TIMI flow grade 0 or I) within the target vessel that persisted and required rescue by a non-assigned treatment strategy (including emergency surgery), or resulted in MI or death. Abrupt closure requires proven association with a mechanical dissection of the treatment site or instrumented vessel, coronary thrombus or severe spasm. Abrupt closure does not connote “no reflow” (due to microvasculature limitation), in which the epicardial artery is patent but had reduced flow. Abrupt closure also does not connote transient closure with reduced flow in which the index treatment application reversed the closure.

**Coronary Dissection** - Refers to a split or a tear in the wall of the [artery](http://www.wikidoc.org/index.php/Artery) which compresses or compromises the [lumen](http://www.wikidoc.org/index.php/Lumen) of the [artery](http://www.wikidoc.org/index.php/Artery) reducing blood flow.

**Coronary Guidewire Dissection** - A coronary dissection where a coronary guidewire is inadvertently positioned in a subintimal position or when stiff-tipped or hydrophilic-tipped guidewires are used to cross highly stenosed or totally occluded arteries.

**Coronary Perforation** - Coronary perforation occurs when a dissection or intimal tear propagates outward sufficient to completely penetrate the arterial wall. This may be caused by pre/post balloon dilatation or post stent deployment where the stent edge causes an edge perforation. Stent edge perforation will range in severity. Ellis classification of coronary perforation:

- Type I - Focal extraluminal crater without extravasation
- Type II - Pericardial or myocardial ‘blush’ without contrast agent
- Type III - Contrast agent ‘jetting’ through a frank (>1 mm) perforation

**Access Site Complication:** A complication occurring at the access site that requires either local intervention or blood transfusion.

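### The relationship categories in Section 7.7.4 and Appendix A exclude each other, so a complication of robotic wire, balloon or stent delivery fits none of them and may be misclassified

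*Protocol*

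**What the plan says.** Section 7.7.4 (Event Relationships) gives the investigator three categories.

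- Procedure related: an event that "results as a consequence of the procedure and is not specifically related to use of the device".
- Device related: an event that "results as a consequence of the use of the device and is not specifically related to the treatment procedure".
- A third category, unrelated, applies where "The adverse event is clearly not related to the device or procedure", because another cause is more plausible and/or the timing does not fit.

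There is no category for both and no rule for choosing between the first two.

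Appendix A defines a procedure-related adverse event a second time. It applies where, in the investigator's judgement, "it is reasonable to believe that the event is not associated with the CorPath GRX System use", and where other products, techniques or drugs needed for the procedure are thought likely to have contributed. Appendix A has no matching definition of device related.

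Three other sections bear on this. Section 7.7.1 states: "Study staff will closely monitor each participant for the development of device and/or procedure related adverse events". Section 7.7.3 opens its reporting list with: "Any of the following device related adverse events will therefore be reported to the manufacturer". Section 5.1.1 gives the intended use of the device as "remote delivery and manipulation of guidewires and rapid exchange balloon/stent catheters, and remote manipulation of guide catheters during percutaneous coronary intervention (PCI) procedures".

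**The concern.** In this trial the device is not an implant whose effects can be separated from the operation. It is the means by which part of the operation is done. Section 7.2.5 has the robot advance the guidewire, deliver the balloon and stent, and retract both. A vessel injury during those steps is the kind of harm the device could plausibly change, and it is also the kind that is most naturally a consequence of device and procedure together.

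Two things are at stake. One is whether a serious event with a device contribution reaches the manufacturer, since the list in Section 7.7.3 is headed by the device-related label. The other is whether a safety table broken down by relationship means the same thing in both arms. In addition, a joint relationship that was never entered on the event form cannot be recovered at analysis, so this cannot be left to a statistical analysis plan.

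**Working it through.** The point concerns definitions. The protocol states no figure to reproduce, so the check is one of logic.

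**Step 1: the three categories as a truth table.** Let P mean that the event is a consequence of the procedure, and D that it is a consequence of device use. On the wording of Section 7.7.4, procedure related = P and not D; device related = D and not P; unrelated = neither P nor D.

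| P | D | Procedure related | Device related | Unrelated |
|---|---|---|---|---|
| no | no | no | no | yes |
| yes | no | yes | no | no |
| no | yes | no | yes | no |
| yes | yes | no | no | no |

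The last row has no category.

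**Step 2: is the last row realistic?** Under Sections 5.1.1 and 7.2.5, use of the device is itself part of the PCI. A dissection from a robotically advanced wire therefore has P = yes and D = yes. The row is not a rare corner case.

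**Step 3: Section 7.7.4 against Appendix A.** The exclusion in Section 7.7.4 turns on a *specific* relation to the device. The one in Appendix A turns on any *association* with CorPath use. Take an event of the procedure that is associated with the device but not specifically related to it. Section 7.7.4 allows it to be procedure related; Appendix A does not. The same event can be classified differently depending on which page is open.

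**Step 4: Section 7.7.1 against Section 7.7.4.** The monitored set in Section 7.7.1 joins the two relationships with an and/or. Section 7.7.4 cannot record the *and*.

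**Step 5: what each forced choice does.**

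- Filed as procedure related: the event stays in the procedure-related count but may fall outside the Section 7.7.3 list.
- Filed as device related: the event reaches Section 7.7.3 but leaves the robotic arm's procedure-related count.

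For any one event these are alternatives; it cannot suffer both.

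**Step 6: the arms compared.** In the standard arm no CorPath is used, so D is always no and every PCI complication can be called procedure related. In the robotic arm the same complication may be moved out of that class or left without one. If true risk were equal and a share s of the robotic-arm complications were moved out, the procedure-related ratio of robotic to standard would read 1 − s instead of 1. The protocol gives neither s nor a complication rate, so this shows how the distortion would arise and not how large it is.

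**The case against.** The strongest reply is that a reader might infer more than the protocol supports. Four points carry weight.

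1. **A biased safety comparison.** It is tempting to conclude that the trial's comparison of procedure-related events will favour the robot. No such comparison is planned. The safety measures in Section 2.4 are MACE and a summary of serious adverse events. MACE is defined without regard to relationship, and endpoint events go to independent adjudication (Section 10.2). Section 8.1 names no analysis of procedure-related rates. This stands: the effect is confined to descriptive tables by relationship, if any are made.

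2. **Device events will be under-reported.** The text does not fix the direction. Appendix A bars an event associated with CorPath from being procedure related, which could push mixed events towards device related and so produce more device reports. This also stands: *may be misclassified* is supportable, and *under-reported* as a flat statement is not.

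3. **Other routes exist.** Section 7.7.3 first defines a serious adverse device effect by seriousness alone, and its near-event wording asks only for association with the device. Device deficiencies have their own route (Sections 7.7.7 and 7.8.1), and Section 7.8.2 cites the regulator's reporting condition. Reasons for manual input or conversion are recorded (Sections 7.2.3 and 7.2.6). These may catch some mixed events. None of them gives such an event a valid label, and the list in Section 7.7.3 still sits under the device-related heading.

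4. **The table can be read as primary attribution.** *Specifically* and the appeal to investigator judgement allow a forced choice, and the and/or in Section 7.7.1 may merely name the set of events to watch. That is a possible working reading. It makes the label depend on the individual investigator, who in a trial described as open-label (Section 8.1) knows the arm, and it does not remove the conflict with Appendix A.

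**Conclusion.** The concern holds as a defect in the event definitions. Section 7.7.4 leaves an event caused by both device and procedure without a category, Appendix A repeats the exclusion at a different threshold, and Section 7.7.1 monitors a class that the categories cannot record. The consequence is possible misclassification in a direction that depends on the investigator. It affects manufacturer reporting under Section 7.7.3 and the between-arm comparability of any descriptive table by relationship.

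MACE, the other named endpoints and the overall summary of serious adverse events do not depend on the label. No numerical size can be derived, because the protocol gives neither a complication rate nor the share of robotic-arm complications with a device contribution. The conclusion rests on reading the definitions as written and on the premise, taken from Sections 5.1.1 and 7.2.5, that robotic delivery is part of the procedure. It is worth correcting because the missing information cannot be rebuilt later.

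**What to change.** - In Section 7.7.4 and Appendix A, remove the clauses that make each relationship exclude the other, and give both places one definition that agrees with Sections 7.7.1 and 7.7.3.
- On the event form, record two separate judgements per event: related to the device (yes/no) and related to the procedure (yes/no). Allow both to be yes; unrelated is then no to both.
- State that any event with device = yes counts as device related for Section 7.7.3.
- If events are tabulated by relationship and arm, use the combined class of device and/or procedure related, which means the same in both arms. No new endpoint or test is needed.

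The cost is a wording change in two places and one extra eCRF field. The small downside is that more events may be labelled device related.

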### Event Expectedness

Adverse events must be assessed as to whether they were anticipated to occur or unanticipated, meaning not anticipated based on current knowledge or found in the protocol, investigator brochure, product insert, or label. Categories are:

| Unanticipated | Nature or severity of the event is not consistent with information about the condition under study or intervention in the protocol, consent form, instructions for use or investigator brochure. |
| --- | --- |
| Anticipated | Event is known to be associated with the intervention or condition under study. |

### Event Severity

Investigators will be asked to report the severity of the adverse event, using the following definitions:

| Mild | Awareness of signs for symptoms but easily tolerated; are of minor irritant; causing no loss of time from normal activities |
| --- | --- |
| Moderate | Discomfort intense enough to cause interference with usual activities |
| Severe | Incapacitating with inability to do work or usual activites |

### Device Deficiency

Any device deficiencies must be reported to the TGA in accordance with Medical device safety reporting.

## **Reporting Procedures**

### General Reporting Requirements (AEs and Device Deficiencies)

- The following criteria must also be adhered to by the Investigator in the electronic data capture (EDC) system:
- Completion of separate Serious/ Adverse Event forms to document each event
- Completion of separate Device Observation forms for each device observation/ deficiency
- The forms must be electronically signed by the Investigator
- Supply to the appropriate authority upon authority’s request, any additional information related to the safety reporting of a particular event

### Reporting Requirements of SADEs

This study does not require serious adverse event reporting as all products used are being used within indication of the listing on the Australia Registry of Therapeutic Goods (ARTG). However in accordance with TGA requirements an automatic condition of inclusion under 5.7 of the [Therapeutic Goods (Medical Devices) Regulations 2002](https://www.legislation.gov.au/Series/F2002B00237) sponsors of a medical device report adverse events or near adverse events to the TGA [Incident Reporting and Investigation Scheme (IRIS)](https://www.tga.gov.au/node/289286).

# Data Management, Statistical Analysis and Record Keeping

## **Statistical Methods**

This is a double-arm, open-label, randomized controlled trial of the CorPath GRX System designed to evaluate the safety and effectiveness of the clinical and technical performance of the CorPath GRX System in the delivery and manipulation of coronary guidewires and stent/balloon catheters, and remote manipulation of guide catheters for use in PCI in comparison to standard of care. The analysis of data collected as part of the RCT will include, but may not be limited to, the Objectives and Measures outlined in Section 3.0 of this protocol. Continuous variables will be summarized using the number of observations, mean, standard deviation, median, min and max values. Categorical variables will be summarized with the number and percent in each category out of the number observed. Two-sided 95% confidence intervals may be calculated and two-sided p-values < 0.05 will be considered statistically significant.

The outcome of patient radiation exposure will be analysed using variance (ANOVA). As each participant may have multiple lesions, the outcome of clinical success at day 3 will be analysed using a two level multilevel models. Logit link will be used with a binomial distribution and restricted maximum likelihood (REML) will be used for estimation. Predictor variables in the models will include treatment group.

Technical success will analysed with Fisher’s exact test, comparing the proportion of participants with technical success between the two groups. Logistic regression will be used to compare technical success accounting for lesion complexity. For all other secondary outcomes, continuous outcomes will be measured using independent t-test (or non-parametric alternative depending on distributional assumptions), and categorical outcomes analysed by Fisher’s exact test. For outcomes measured repeatedly over time, multilevel models with an appropriate link functions will be used for analysis.

All statistical analyses will be performed using SAS software (version 9.4) or other widely accepted statistical or graphical software.

A total sample of 300 patients (150 in each group) is sufficient to detect a 20% reduction in radiation exposure to the patient during PCI, assuming a mean radiation exposure of 1284 mGy with standard deviation 180 mGy in the control group, and a standard deviation of 142.83 in the intervention group (29) with greater than 99% statistical power, and two sided statistical significance of 5%.

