## **Other Measures/ Procedural Characteristics**

The objective of this study is to compare standard PCI with technology-assisted PCI to collect real-world data. When the PCI is being performed in conjunction with a diagnostic procedure, all efforts should be made to isolate the PCI procedural characteristics from the diagnostic procedure. At the end of the diagnostic procedure or alternatively to coincide with the PCI procedure time record the contrast, fluoroscopy time, DAP & AK at the end of the diagnostic procedure. When the PCI procedure is finished, record the values for these characteristics accumulated during the PCI procedure and not the diagnostic procedure. Procedures will be identified as staged (PCI only) or ad-hoc (LHC possible PCI). Any requirement to move from technology-assisted PCI to standard care will also be captured.

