### Participant and Staff Radiation Exposure

DAP (dose-area-product) and cumulative dose/air kerma, as recorded during the PCI procedure. Radiation exposure to the patient and staff will be measured by personal dosimeters (Polimaster PM1610) placed at the left shoulder.

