## **Schedule of Events**

| **Exam/ Test/ Data Collection** | **Screening** | **Index**  **Procedure** | **Day 3/ discharge** | **Day 30**  **(±5 days)** | **EOS / Day 365**  **(±14 days)** |
| --- | --- | --- | --- | --- | --- |
| Informed consent | X | X |  |  |  |
| Medical history | X |  |  |  |  |
| Demographics | X |  |  |  |  |
| Vital signs including height, weight^1^ | X | X^6^ | X^6^ |  |  |
| Physical examination | X^1^ |  | X |  |  |
| 12 lead ECG | X^4^ |  | X |  |  |
| non-cardiac laboratory assessments | X |  | X |  |  |
| Cardiac enzymes | X^2^ |  | X^3^ |  |  |
| Inclusion/ exclusion criteria | X |  |  |  |  |
| Randomisation |  | X |  |  |  |
| PCI |  | X |  |  |  |
| Dosimeter reading |  | X |  |  |  |
| Fluoroscopy reading |  | X |  |  |  |
| Lesion assessment |  | x |  |  |  |
| Time of procedure |  | X |  |  |  |
| Contrast usage |  | X |  |  |  |
| Equipment usage |  | X |  |  |  |
| Concomitant medications | X | X | X | X | X |
| Adverse Events^5^ |  | X |  |  |  |
| Health care resource usage |  | X | X | X | X |
| Event Assessment |  | X | X^5^ | X^5^ | X^5^ |
| Complete Case Report Form | X | X | X | X | X |

^1^ Within 30 days of index procedure

^2^ Pre-procedure cardiac enzymes within 7 days of index procedure, if collected.

^3^ Post-procedure cardiac enzyme collection is left to the discretion of the investigator and shall be dictated by the participant’s clinical symptoms.

^4^ Post-procedure 12-lead ECG: it is recommended that an ECG be performed at the time of discharge but is not required for the protocol.

^5^ Related to procedure, intervention or Adverse Event of Special Interest (MACE)

^6^ height and weight only required at screening

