### Data to be collected prior to initiating PCI

- Operator and assistant details
- Arterial access site and side
- Procedure start time (Sheath insertion)
- PCI Start Time (Guide Catheter Insertion)
- American Heart Association/American College of Cardiology lesion classification

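### Patient radiation, the only outcome the trial is sized on, is assigned a plain ANOVA although likely predictors of dose are already collected and could be adjusted for

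*Protocol*

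**What the plan says.** Section 8.1 (Statistical Methods) gives one sample-size statement: "A total sample of 300 patients (150 in each group) is sufficient to detect a 20% reduction in radiation exposure to the patient during PCI". The planning values that it rests on are worded thus: "assuming a mean radiation exposure of 1284 mGy with standard deviation 180 mGy in the control group, and a standard deviation of 142.83". The second SD is that of the robotic arm. Significance is two-sided at 5%, and the claimed power is above 99%. No other outcome is sized.

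For the analysis of that outcome the section says: "The outcome of patient radiation exposure will be analysed using variance (ANOVA". It names no covariate, transformation or fallback. Two other provisions in 8.1 are more detailed. Technical success is compared by Fisher's exact test and also by logistic regression that accounts for lesion complexity. The other secondary continuous outcomes get a t-test or a non-parametric alternative, depending on distribution.

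Several candidate covariates are already in the data collection:

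- Section 3.3 (Schedule of Events) lists "Vital signs including height, weight" at screening.
- Section 2.6 states: "Procedures will be identified as staged (PCI only) or ad-hoc (LHC possible PCI".
- Section 7.2.2, on data collected before PCI starts, lists "American Heart Association/American College of Cardiology lesion classification".

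Section 2.6 also asks for PCI values to be separated from those of any diagnostic procedure. Section 2.6.5 lists dose-area product and cumulative dose/air kerma, and adds: "Radiation exposure to the patient and staff will be measured by personal dosimeters (Polimaster PM1610) placed at the left shoulder".

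**The concern.** With two arms and no covariates, ANOVA is the equal-variance two-sample t-test. All variation in dose due to body size, lesion complexity or type of procedure stays in the error term. Eligibility is broad: age 18 to 85, any clinical indication for PCI, and no limit on weight or lesion class beyond suitability for robotic PCI. Section 8.1 also allows several lesions per participant. In such a population much of the spread in dose may be predictable before the procedure starts.

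At stake is the precision of the trial's one powered comparison. The planning SDs are 14% of the means, and the protocol shows no power for any other SD. If dose varies more than planned, the unadjusted test has the least protection. If dose is also skewed, this outcome alone lacks the fallback that the other secondary continuous outcomes have. The hypothesis is a percentage reduction, while the power inputs are means and SDs in mGy.

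**Working it through.** **Inputs from section 8.1.** Control mean 1284 mGy; SDs 180 and 142.83 mGy; reduction 20%; 150 per arm; two-sided alpha 5%.

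**Step 1: reproduce the stated power.**

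- Difference: 0.20 × 1284 = 256.8 mGy, so the intervention mean is 1027.2 mGy.
- Coefficients of variation (CV): 180/1284 = 14.0%; 142.83/1027.2 = 13.9%.
- Root-mean-square SD: √[(180² + 142.83²)/2] = √26400.2 = 162.5 mGy.
- Standardised difference: 256.8/162.5 = 1.58.
- Standard error at 150 per arm: 162.5 × √(2/150) = 18.8 mGy; 256.8/18.8 = 13.7.

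Power is essentially 100%, so the stated figure reproduces. With the noncentral t distribution, 15 per arm give 98.7% and 16 per arm give 99.1%. The planned 150 is roughly ten times what this calculation needs.

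**Step 2: how large can the SD be?** Solve the two-sample t-test power for a common SD, with difference 256.8 mGy and 150 per arm.

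| Power | Largest common SD | As % of 1284 | Multiple of 162.5 |
|---|---|---|---|
| 99% | 517 mGy | 40% | 3.2 |
| 90% | 684 mGy | 53% | 4.2 |
| 80% | 791 mGy | 62% | 4.9 |

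The normal approximation gives 519, 686 and 794 mGy, which is the same for practical purposes.

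**Step 3: what adjustment gains.** If covariates explain a share R² of the variance, the residual SD is SD × √(1 − R²). The documents give no R², so the values here are assumptions.

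| Common SD | Unadjusted | R² = 0.10 | R² = 0.25 | R² = 0.30 |
|---|---|---|---|---|
| 517 mGy | 99.0% | 99.5% | 99.9% | 99.9% |
| 684 mGy | 90.0% | 92.7% | 96.3% | 97.2% |
| 791 mGy | 80.0% | 84.0% | 89.9% | 91.8% |

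At R² = 0.25 the residual SD is √0.75 = 0.866 of the original. The SD limits in Step 2 become 517/0.866 = 597, 684/0.866 = 790 and 791/0.866 = 913 mGy. Since 1/(1 − 0.25) = 1.33, 300 adjusted patients are worth about 400 unadjusted ones. At the planned SDs there is no power left to gain; the 95% interval half-width falls from about 37 mGy (1.97 × 18.8) to about 32 mGy (37 × 0.866).

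**Step 4: if dose is skewed.** I assumed log-normal dose with the same CV in both arms and a ratio of 0.8. Unadjusted figures are from 10,000 simulated trials per CV; the adjusted column is computed from the t-test formula.

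| Assumed CV | Raw scale | Log scale | Log scale, R² = 0.25 |
|---|---|---|---|
| 50% | 97% | 98% | 99.7% |
| 70% | 79% | 86% | 94% |
| 90% | 58% | 70% | 82% |

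Steps 2 and 4 are not interchangeable. Step 2 holds the SD equal in both arms. Step 4 holds the CV equal, so the intervention SD is smaller.

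**The case against.** The strongest reply is that nothing here is broken. ANOVA at 150 per arm is a valid test of mean dose, and the alleged loss is of efficiency only. At the planned SDs power is near 100% with or without covariates. The protocol says that 300 patients are sufficient, not that they are the minimum, and there are clinical, technical, safety and cost outcomes as well. All of this stands.

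A second reply is that unadjusted and raw-scale are read from silence, and that covariates and transformations are often left to a statistical analysis plan. This stands in part. But section 8.1 does not defer such matters generally: it states an adjustment for one outcome and a distributional fallback for others, and gives neither to the outcome that carries the sample size.

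A third reply concerns the remedy. The log scale changes the estimand from a difference in mGy to a ratio of geometric means, so it should not be mandatory. Lesion class belongs to a lesion, and participants may have several, so a rule is needed to reduce it to one value per patient. Both are accepted.

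A reader might infer that the power claim is fragile. The figures do not show that: 99% power survives a threefold rise in SD, and the protocol contains no evidence of a CV above 40%. A reader might also suspect that the SDs are scaled values or standard errors, because 142.83 = 0.7935 × 180. That cannot be judged without the cited source. It is weak evidence too: about one in nine two-decimal numbers is an exact four-decimal multiple of 180, and scaling by the planned reduction would give 0.8 × 180 = 144. Finally, the choice of dose measure is mostly a matter of detail, since the unit mGy in the sizing already rules out dose-area product.

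**Conclusion.** The point holds as an available improvement, not as an error. The outcome on which the trial is sized has a less developed analysis than outcomes of lesser weight, while variables likely to explain part of the dose are collected anyway. The stated power above 99% is correct on its inputs and robust to SDs about 3.2 times the planned value.

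The size of the gain depends on the true SD. At the planned SDs it is about 5 mGy in the interval half-width. At a common SD of 684 to 791 mGy, with R² = 0.25, it is 6 to 10 percentage points of power. That rests on two assumptions that the documents neither support nor exclude: an SD well above plan, and covariates that explain about a quarter of the variance. The further gain from the log scale also assumes a skewed, roughly log-normal dose.

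**What to change.** In section 8.1, replace the ANOVA of patient radiation with ANCOVA of PCI-phase air kerma (mGy) on arm, weight or BMI, staged or ad-hoc status, and the ACC/AHA class of the most complex treated lesion. Use the class recorded before PCI begins. Section 7.2 allows randomisation up to 24 hours before PCI, so the operator may know the arm when grading; grade from the angiogram before the arm is disclosed where possible.

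Because the hypothesis is a percentage reduction, name the log-scale version of the same model, reported as a geometric mean ratio with 95% CI, as the pre-specified alternative if dose is skewed. State in advance how skewness will be judged.

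In the sample-size paragraph, check both SDs against the cited source and add one sentence: with 150 per arm and no adjustment, power is at least 99% up to a common SD of about 517 mGy, 90% up to 684 and 80% up to 791.

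The cost is wording only, with no extra patients, visits or data. The small downside is that the log-scale alternative, if used, reports a ratio instead of a difference in mGy.
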